### 2.1 Design, participants and procedures

The protocol has a prospective, two-arm, open-label, non-randomized study design (Fig 2). In a real-world clinical setting, patients will be consecutively enrolled according to the following eligibility criteria: 18 years of age or older; diagnosis of acquired brain injury (ABI; e.g., TBI, stroke), Parkinson’s Disease (PD) or orthopaedic disease (i.e., total hip/knee arthroplasty) requiring rehabilitation intervention; absence of a severe clinical condition (i.e., chronic heart failure at class IV according to the New York Heart Association classification—NYHA-IV, ischemic heart disease at class IV according to the Canadian Cardiovascular Society classification—CCS-IV, neoplastic diseases, acute respiratory diseases); no severe cognitive impairment (screened with the Montreal Cognitive Assessment–MoCA ≤ 15.5) [40]; no language disorders (e.g., aphasia); absence of severe mental health condition or psychiatric disorder (evaluated according to the Diagnostic and Statistical Manual of Mental Disorders—DSM-V) potentially compromising participation in the study; absence or withdrawal of the informed consent to participate.

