At hospital admission (or after clinical stabilization), patients will be screened according to the criteria described above by a panel consisting of physical and rehabilitation medicine specialists and researchers. Those considered eligible will undergo a multidimensional baseline evaluation including the functional status (i.e., disability, autonomy in the ADLs, risk of falls), cognitive functioning (i.e., attention, executive functions, reaction times, phonemic fluency), HRQoL, and psychological characteristics (i.e., quality of life satisfaction, anxiety and depression symptoms). After the intervention (4 weeks), patients will undergo the same evaluation battery to estimate pre- post-treatment differences and their rehabilitation experiences will be assessed. Participants will be divided into two subgroups, depending on their rehabilitation program. The first group will include patients who underwent conventional treatment exclusively, while the second group will be composed of those who participated in both conventional and RAT or VR-based rehabilitation. The latter, at post-intervention, will be further asked to evaluate the experience of use of the devices and the perceived usability (through a mixed-method approach), as well as the related perceived psychosocial impact. Technology evaluation will be also extended to the therapists involved in the rehabilitation programs. These will undergo mixed-method evaluation (i.e., questionnaire and semi-structured interview) aiming to collect data on the perceived usability of devices from the healthcare professional’s point of view. In conclusion, at six months following the rehabilitation program, all patients will be contacted by telephone and asked to provide information concerning their perceived functional status, level of autonomy in the ADLs, perceived HRQoL, and anxiety and depression symptoms.

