### 2.2 Intervention and technological devices description

All patients will receive conventional treatment consisting of two daily one-hour sessions over 4 weeks, including traditional rehabilitation activities like range of motion exercises (passive, active assisted and active), progressive resistive exercises, balance and strength training, and aerobic conditioning. For the patients additionally participating in the RAT or VR-based rehabilitation, part of the duration of the whole treatment will be dedicated to the use of the devices, resulting in the same amount of rehabilitation for all participants. According to the technological device implemented (i.e., RAT or VR-based treatment), the intervention procedures and the related eligibility to participate will be checked according to the technology-specific guidelines and recommendations as appropriate [41–43]. The intervention will be delivered following the routine multidisciplinary clinical practice of the Institution where the study will be conducted [44]. Specifically, for each patient, the clinical care pathway will be based on the integration of the International Classification of Diseases (ICD) and the International Classification of Functioning Disability and Health (ICF) models as recommended by the WHO framework [45]. Therefore, adopting a biopsychosocial approach, the rehabilitation procedures will be adapted according to the patient’s medical diagnosis, disability severity, and rehabilitation objectives in favor of an individualized rehabilitation project and program. Therefore, if necessary, patients may undergo parallel rehabilitation activities that will involve different healthcare professionals (i.e., occupational therapists, speech therapists, psychologists).

Technology-based rehabilitation will be delivered through the following exoskeleton or non-immersive VR devices.

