### 2.3 Data collection

Following preliminary collection of the socio-demographic (i.e., age, gender, living conditions, marital status, occupation, caregiver identification, and education) and clinical (i.e., BMI, primary diagnosis, comorbidities, health-related risk factors, and COVID-19-related anamnesis) characteristics, patients will undergo a multidimensional evaluation. This will include the functional status, cognitive functioning, perceived HRQoL and psychological aspects. All patients will be also asked to report any prior experience in using technological devices during rehabilitation. Moreover, the same information will be collected from the therapists involved, along with their individual socio-demographic and occupation-related data (i.e., age, gender, occupation, and overall seniority).

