### 2.6 Statistical analyses

Descriptive statistics will be conducted on participants’ socio-demographic and clinical characteristics, functional status, cognitive functioning, and HRQoL, and psychological status. Explorative analyses will be then conducted to estimate pre- post-treatment changes and long-term effects concerning the multidimensional evaluation performed. Particularly, these will be carried out by comparing patients who share the same medical disease and who experienced the use of the same technological device during rehabilitation. Within- and between-group pre- post-intervention differences will be tested with the paired-samples *t*-test and independent samples *t*-test, respectively. Additionally, a repeated-measures ANOVA test will be used to assess the longitudinal trajectories. Regarding technology evaluation, descriptive statistics will be conducted on devices usability, experience of use and psychosocial impact. Furthermore, post-hoc analyses will be performed to estimate the differences on technology evaluation in relation to the clinical condition and severity of participants. As for therapists’ devices experience of use, the semi-structured interviews will be analysed through inductive thematic analysis [73]. In conclusion, association analyses (e.g., correlations, regressions) will be carried out to explore the inter-relationships among all the variables measured. The Statistical Package for the Social Sciences (SPSS, version 28.0) will be implemented for data analyses. Sample size adequacy was estimated by resorting to power analysis [74], using G*Power Software Version 3.1.9.7 [75] on a repeated-measures ANOVA (within-between interaction) with three measurements, two groups, and a correlation among repeated measures of 0.5 (power: 0.80; α = 0.05). The required sample size to detect small-medium effect sizes (f = 0.20) was a minimum of 42 patients.

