### 3.1 Limitations

The present study protocol presents some design-related limitations. The first limit is the absence of randomization. However, although randomized control trials represent essential research tools with strong internal validity, it must be recognized that they may suffer from low generalizability to real life conditions [84]. For this reason, the present study protocol was outlined within a real-world clinical setting, where the actual effectiveness of technology will be explored [85]. Another limitation is the single-center design and the limited sample size calculated. Regarding the latter, even reaching the required sample size, the evidence from the reports that will be generated will not be sufficient to draw generalizable conclusions and should be considered as preliminary. Accordingly, there is a need for multicenter and large-scale studies in order to generalize the benefits of RAT and VR-based rehabilitation particularly on outcomes that are not strictly related to motor functioning. In conclusion, the use of self-report evaluation may be limiting for different reasons, including the risk of false-positive, lack of sensitivity to change, and social desirability bias. Nonetheless, this evaluation approach was preferred given some advantages like good clinical and research applicability, high practicality of use, and satisfactory cost-effectiveness.

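### The between-arm tests carry no covariates although the arms are non-randomised, so within-diagnosis differences in severity, age or device eligibility can be read as a device effect

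*Protocol article*

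**What the plan says.** Section 2.1 is explicit about the design: "The protocol has a prospective, two-arm, open-label, non-randomized study design". It adds that "Participants will be divided into two subgroups, depending on their rehabilitation program". Membership is described by treatment undergone: "The first group will include patients who underwent conventional treatment exclusively"; patients who also had device-based treatment form the other arm.

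Section 2.2 ties the programme to patient characteristics. For device treatment, "the intervention procedures and the related eligibility to participate will be checked according to the technology-specific guidelines and recommendations as appropriate". Programmes are also individualised on diagnosis, disability severity and rehabilitation goals.

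Section 2.6 then fixes the tests: "Within- and between-group pre- post-intervention differences will be tested with the paired-samples" t-test and the independent-samples t-test, in that order, plus a repeated-measures ANOVA. No covariate, matching or weighting is mentioned. The one control stated is that comparisons are made among patients with the same disease and the same device. Regressions appear only as a way to explore associations among all the variables.

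Section 2.3 collects age and education, clinical data ("BMI, primary diagnosis, comorbidities, health-related risk factors, and COVID-19-related anamnesis"), and baseline function, cognition, quality of life and mood. Section 3.1 concedes that "The first limit is the absence of randomization", and answers with the wider applicability of real-world data.

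**The concern.** Allocation depends on things that plausibly predict recovery: severity, treatment goals and fitness for a device. An unadjusted comparison of such arms estimates the device effect plus whatever prognostic difference comes with allocation, and a larger sample would not remove that second part.

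The same-disease restriction deals with the mix of brain injury, Parkinson's disease and arthroplasty. Within one diagnosis, the arms can still differ in severity, age, cognition, comorbidity and device eligibility. The same-device condition cannot balance the arms, because the conventional arm uses no device.

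The contrast matters to this study. The abstract announces within-between interaction effects, the sample size in 2.6 is set on that interaction, and 3.1 says that the effectiveness of the technology will be explored. Variables that could reduce the confounding are already being recorded.

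**Working it through.** **The plan's own figure.** Inputs from 2.6: three measurements (m), two groups (k), correlation ρ = 0.5, f = 0.20, α = 0.05, power 0.80. Sphericity is assumed, as nothing is stated.
- Noncentrality λ = N f² m / (1 − ρ) = 42 × 0.04 × 3 / 0.5 = 10.08
- Degrees of freedom: (k − 1)(m − 1) = 2 and (N − k)(m − 1) = 80
- Power is 0.803 at N = 42 and 0.782 at N = 40

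The stated minimum of 42 reproduces. The issue lies in the analysis, not in this arithmetic.

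**What the interaction test does with a prognostic difference.** With the same formula at N = 42 and no device effect, suppose the arms' courses differ for prognostic reasons alone by f = 0.10, 0.15 or 0.20. The interaction is then significant in about 27%, 54% and 80% of studies.

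**What the t-test on change does.** The article gives no imbalance and no allocation ratio, so the gap d (in baseline SD) and 21 per arm are assumptions. There is no device effect.

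*Mechanism A: allocation acts through the measured baseline score.* The post value is ρ × baseline plus independent noise.
- Spurious difference in change = (1 − ρ) d in size, so 0.15, 0.25 and 0.40 SD for d = 0.3, 0.5 and 0.8
- Variance of change = 2(1 − ρ) = 1, so the t-test noncentrality is 0.5 d × √(21/2) = 0.49, 0.81 and 1.30 on 40 df

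*Mechanism B: a stable difference between the arms, with parallel courses.* The gap d is present equally at baseline and after treatment.
- Expected difference in change = 0, so the t-test keeps its level
- Baseline-only ANCOVA subtracts just ρ d, leaving a bias of (1 − ρ) d = 0.15, 0.25 and 0.40 SD

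Simulated rejection rates (4,000 studies per gap for A, 6,000 for B), nominal 5%:

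| Baseline gap | A: change t-test | A: baseline ANCOVA | B: change t-test | B: baseline ANCOVA |
|---|---|---|---|---|
| 0.3 SD | 8% | 6% | about 5% | 8% |
| 0.5 SD | 13% | 5% | about 5% | 14% |
| 0.8 SD | 25% | 5% | about 5% | 27% |

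Under A, the sign of the bias is opposite to the baseline gap: the arm that starts higher appears to gain less. The error can therefore favour or penalise the device.

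**The case against.** Four arguments carry weight.

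1. **The plan does restrict its comparisons.** This stands as far as it goes. A reader might infer that a different mix of diagnoses will bias the contrast. Section 2.6 compares patients with the same disease, so that holds only if diagnoses are pooled.
2. **Baseline ANCOVA is not a neutral remedy.** This stands. Under mechanism B, the planned test is unbiased and ANCOVA on the baseline value alone is not. The article does not say which mechanism applies. This is a reason to adjust for severity and age as well, and to show both analyses; it is no reason to rely on the unadjusted test alone.
3. **The analyses are called explorative and the results preliminary.** This lowers the stakes. However, 3.1 attaches the preliminary status to the single-centre design and sample size, and meets the lack of randomisation with generalisability. Neither addresses confounding.
4. **Covariates may be listed in a fuller plan.** Possible, and naming a repeated-measures ANOVA does not rule them out. But this text does name the between-arm tests, and an independent-samples t-test has no place for a covariate.

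A reader might also infer, from arms described by treatment undergone, that patients enter the device arm because they recover early. The documents do not support this: 2.2 does not say when device eligibility is checked, and 2.1 places study screening at admission or after stabilisation.

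**Conclusion.** The point holds as a weakness of a stated method. Arms formed by programme, severity and device eligibility are compared without covariates, so prognostic differences within a diagnosis remain in the contrast and can be taken for a device effect.

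Its size cannot be fixed from the document. With 21 per arm, ρ = 0.5 and allocation through the baseline score, gaps of 0.3 to 0.8 SD raise the false-positive rate of the change-score t-test from 5% to between 8% and 25%. Under a stable difference with parallel courses it stays at 5%. The gaps and the equal split are assumptions.

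Two stronger readings go too far. It does not follow that the arms will in fact differ, or that adjustment would remove all bias: it reaches measured confounding only. Nor can baseline adjustment serve every outcome, because the Global Perceived Effect item and the rehabilitation-experience questionnaire (CCRQ) are given only after treatment.

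**What to change.** In section 2.6:
- **Outcomes with a baseline value:** make the main between-arm contrast an ANCOVA or mixed model, adjusted for the baseline value of the outcome, age, and baseline FIM motor or another severity measure. Add diagnosis if diagnoses are pooled. Keep the unadjusted change-score t-test as a sensitivity analysis, and comment where the two disagree.
- **Post-only outcomes given in both arms (Global Perceived Effect, CCRQ):** adjust for age and baseline function only.
- **Within-arm changes:** report them descriptively.
- **Wording:** describe the contrast as an adjusted association and state that unmeasured confounding remains.

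The cost is analysis text and a few degrees of freedom. No extra patients or measurements are needed, and data collection is still under way. With a minimum of 42 patients divided by disease and device, the covariate set must stay small, with the baseline value of the outcome first.

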## 3. Discussion

The present work aimed to describe a study protocol exploring the short- and long-term perceived biopsychosocial effects and the experience of use of robotic and VR devices in patients undergoing neuromotor rehabilitation. For this purpose, a prospective multidimensional evaluation investigating the patient’s functional status (i.e., disability, autonomy in the ADL, risk of falls), cognitive functioning (i.e., attention and executive functions), perceived HRQoL, and psychological status (i.e., anxiety and depression symptoms) was outlined. Besides, the psychosocial impact of the technological devices implemented will be explored and an evaluation of the perception of their usability and experience of use will be carried out by considering both patients’ and therapists’ perspectives, through a mixed-methods approach.

Based on the aims of this study protocol and according to the existing literature, it is expected that the present contribution may corroborate the evidence of prior works on patient’s motor recovery highlighting the added value of integrating robotics and VR in neuromotor rehabilitation programs. Most importantly, the development of the current study protocol was aimed at giving more centrality to the psychological dimension of patient’s health, contributing overall to deepen knowledge on the short- and long-term effectiveness of RAT and VR-based rehabilitation beyond motor improvement. Furthermore, the mixed-methods investigation of the perception of the technology implemented, in terms of experience of use and perceived usability, not only will shed light on devices’ technical strengths and limitations with a view to improved technology deployment, but it will also provide crucial evidence into patient’s attitude towards technology-based rehabilitation, including therapy engagement, adherence, and efficacy.

So far, diverse clinical trials protocols have been recently developed with the purpose of estimating the motor and functional benefits of RAT and VR-based therapy in different clinical populations [76–83]. Nevertheless, it must be noted that for the most, although factors like patient’s mental status or technology acceptance were investigated, these were considered as secondary outcomes essentially. The added value of the present protocol lies therefore in the attempt to better understand the psychological impact and the experience of use of technological devices in neuromotor rehabilitation, thereby providing a deeper knowledge and discussion, net of patient’s motor and functional changes.

### 3.1 Limitations

The present study protocol presents some design-related limitations. The first limit is the absence of randomization. However, although randomized control trials represent essential research tools with strong internal validity, it must be recognized that they may suffer from low generalizability to real life conditions [84]. For this reason, the present study protocol was outlined within a real-world clinical setting, where the actual effectiveness of technology will be explored [85]. Another limitation is the single-center design and the limited sample size calculated. Regarding the latter, even reaching the required sample size, the evidence from the reports that will be generated will not be sufficient to draw generalizable conclusions and should be considered as preliminary. Accordingly, there is a need for multicenter and large-scale studies in order to generalize the benefits of RAT and VR-based rehabilitation particularly on outcomes that are not strictly related to motor functioning. In conclusion, the use of self-report evaluation may be limiting for different reasons, including the risk of false-positive, lack of sensitivity to change, and social desirability bias. Nonetheless, this evaluation approach was preferred given some advantages like good clinical and research applicability, high practicality of use, and satisfactory cost-effectiveness.

### 3.2 Implications

Relevant practical implications should be noted. The study protocol described was developed adopting a multidimensional and multidisciplinary approach. This choice comes from the intention to put the study into a biopsychosocial framework, where multiple patients’ health-related domains, and their complementarity, are considered throughout technology-based rehabilitation programs [86]. This approach may help to expand the perspective on patient recovery within this ever-growing intervention procedure, consequently providing a deeper understanding on the definition of more tailored recovery pathways. Following this line, also the involvement of different pathologies with different degrees of severity, as well as the use of different technological devices will contribute to obtaining more heterogenous findings and deeper knowledge on how to improve technology implementation and its effectiveness. In conclusion, alongside the continuously aging population and the related increase in chronic diseases and multimorbidity, providing more complex intervention guidelines along with optimal and tailored recovery has become of paramount concern [87]. Accordingly, high technology may represent a valuable tool to respond to the emerging public health challenges and, more broadly, a practical solution for healthcare sustainability issues.
